### Outcome Measures

The primary outcome is the percentage change in PaCO_2_ from baseline to 60 minutes after initiation of therapy. Baseline is defined as the pretreatment ABG obtained before initiation of the assigned therapy (HVNI or NIPPV). This ensures that the primary outcome reflects the ventilatory effect of the intervention itself. The 30- and 60-minute assessment time points are measured from the time of therapy initiation. The ABG results and other variables (Table 1) to be collected will be documented in real time on paper-based CRFs by trained study investigators.

**Table 1. T1:** Summary of recorded patient variables in a noninferiority randomized controlled trial comparing high-velocity nasal insufflation (HVNI) vs noninvasive positive pressure ventilation (NIPPV) for type 2 respiratory failure in adult emergency department patients at National University Hospital, Singapore.

Variables	Measure
Primary outcome measure	Change in PaCO_2_^a^ at 60 min obtained after initiation of HVNI or NIPPV compared to baseline (before initiation of therapy)
Secondary outcome measures	Change in PaCO_2_ at 30 min compared to baseline Changes in respiratory rate 30 and 60 min after initiation of HVNI or NIPPV Modified Borg Dyspnea Scale at 30 and 60 min Treatment failure Conversion to another modality of oxygenation Requirement for intubation in the emergency department Adverse events due to therapy
Demographics	Age Gender Ethnicity BMI
Comorbidities	Congestive cardiac failure Ischemic heart disease Atrial fibrillation Chronic obstructive pulmonary disease Asthma Obstructive sleep apnea Diabetes mellitus Bronchiectasis Restrictive lung disease Neuromuscular disease Opioid or benzodiazepine use
Vital signs	Temperature Heart rate Respiratory rate Systolic and diastolic blood pressure Mean arterial pressure Glasgow Coma Scale
Investigations	Chest x-ray findings Arterial blood gas results at 0, 30, and 60 min
Clinical course and secondary clinical outcomes	Emergency department diagnosis Hospital inpatient discharge diagnosis Length of intensive care unit stay (if any) Length of hospital stay Inpatient mortality

a PaCO_2_: partial pressure of carbon dioxide.

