Percentage change (relative difference) as the primary outcome was selected to account for the wide range of baseline PaCO_2_ values expected in a heterogeneous, all-cause T2RF population. An absolute change in PaCO_2_ may disproportionately favor patients with higher baseline values as they have greater room for absolute reduction. The percentage change normalizes the treatment effect relative to each patient’s starting value, facilitating more equitable comparison across the spectrum of disease severity. To address the potential limitation of relative outcomes, a prespecified sensitivity analysis using absolute change in PaCO_2_ at 60 minutes will be conducted to confirm the robustness of the primary finding.

Secondary outcomes include the following: percentage change in PaCO_2_ from baseline to 30 minutes; change in respiratory rate at 30 and 60 minutes; modified Borg Dyspnea Scale (0-10) at 30 and 60 minutes [24]; proportion of treatment failure (as defined above), conversion to another modality of oxygenation, and need for intubation in the ED; adverse events due to therapy rendered (eg, facial pressure injury, vomiting, or aspiration); length of intensive care unit (ICU) and hospital stay; and inpatient mortality. Inpatient mortality will be assessed at hospital discharge. ICU length of stay (if applicable) and total hospital length of stay will be recorded in days from the date of ED presentation to the date of ICU discharge and hospital discharge, respectively. These data will be abstracted from the electronic health record (EHR) following patient discharge.

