### Sample Size

A total of 84 patients (42 per group) will be enrolled to provide 80% power and one-sided α of 2.5% to demonstrate noninferiority [25] assuming an SD of 6.65% for percentage change in PaCO_2_ levels before and after treatment [26] and a noninferiority margin of 4.3%. The sample size includes an estimated 10% allowance for missing primary end point data. The noninferiority margin of a 4.3% absolute difference in percentage change was informed by clinician judgment (number of specialist accredited [board-certified] emergency physicians, n=14) of clinically acceptable differences and literature on PaCO_2_ responses to NIPPV. For example, emergency physicians opined that a change from 70 mm Hg to 63 mm Hg using HVNI (−10.0%) was considered noninferior to a change in PaCO_2_ from 70 mm Hg to 60 mm Hg after treatment with NIPPV (−14.3%).

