### Statistical Analysis Overview

The primary analysis will follow an intention-to-treat approach, with supportive per-protocol analysis excluding major deviations (eg, early crossovers or missing postbaseline ABG values) and a safety set analyzed as treated. The main end point, percentage change in PaCO_2_ at 60 minutes, will be assessed using analysis of covariance (ANCOVA) adjusting for baseline PaCO_2_ and prespecified covariates (eg, etiology, baseline pH, and age). Noninferiority will be concluded if the upper bound of the 2-sided 95% CI for the HVNI–NIPPV adjusted difference is below the 4.3% margin. A prespecified sensitivity analysis will repeat the primary ANCOVA model using absolute change in PaCO_2_ at 60 minutes as the dependent variable to assess whether the conclusions are robust to the choice of relative vs absolute outcome metric. Secondary endpoints (percentage PaCO_2_ changes at 30 minutes, respiratory rate, and modified Borg Dyspnea Scale) will use similar adjusted models, whereas binary outcomes (treatment failure, intubation, and adverse events) will be compared using chi-square or Fisher exact tests and logistic regression, and length of stay and mortality will be assessed via nonparametric or time-to-event and logistic methods. Missing data handling will focus primarily on the primary outcome (percentage change in PaCO_2_ at 60 minutes). Missing 60-minute ABG results may occur due to early treatment crossover, intubation before the 60-minute time point, patient refusal of repeat ABG, or technical failure of the ABG analyzer. Multiple imputation by chained equations will be performed, with the imputation model including baseline PaCO_2_, baseline pH, treatment arm, age, etiology, respiratory rate, and 30-minute PaCO_2_ (if available). A minimum of 20 imputed datasets will be generated, and results will be pooled using the Rubin rules.

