Sensitivity analyses will include (1) complete-case analysis (excluding participants with missing primary outcome data) and (2) worst-case imputation for the HVNI arm (assigning the worst observed percentage change to missing values in the HVNI arm and the best observed percentage change to missing values in the NIPPV arm), which is a conservative approach for noninferiority trials. Baseline covariates with missing data (expected to be minimal) will be handled through multiple imputation within the same multiple imputation by chained equations framework. Missing secondary outcomes will be analyzed using available data, with the extent of missingness reported for each outcome. Secondary endpoints will be treated as exploratory without formal multiplicity adjustment.

Prespecified exploratory subgroup analyses will be conducted to assess potential heterogeneity of treatment effect. Subgroups will include (1) COPD vs non-COPD etiology, (2) baseline PaCO_2_ strata (eg, 45‐60 mm Hg vs >60 mm Hg), and (3) baseline pH strata (eg, 7.25‐7.35 vs <7.25). Subgroup effects will be evaluated by including interaction terms (subgroup × treatment) in the primary ANCOVA model. These analyses are exploratory and hypothesis generating; the trial is not powered for subgroup comparisons, and results will be interpreted with caution.

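### ICU length of stay is defined from ED presentation, so the rule measures time to ICU discharge and overstates ICU stay for anyone admitted to the ICU on a later date

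*Protocol article*

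**What the plan says.** The text of the Outcome Measures section includes "length of intensive care unit (ICU) and hospital stay; and inpatient mortality" among the secondary outcomes. Table 1 has a row for clinical course and secondary clinical outcomes that lists "Length of intensive care unit stay (if any) Length of hospital stay Inpatient mortality", with no start or end date.

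The only operational definition is one sentence in Outcome Measures. It gives the start for both durations: "ICU length of stay (if applicable) and total hospital length of stay will be recorded in days from the date of ED presentation". It then gives the two ends; the durations are "recorded in days from the date of ED presentation to the date of ICU discharge and hospital discharge, respectively". The values are to be abstracted from the electronic health record after discharge.

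Under Statistical Analysis Overview, "length of stay and mortality will be assessed via nonparametric or time-to-event and logistic methods". The same section adds: "Secondary endpoints will be treated as exploratory without formal multiplicity adjustment".

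**The concern.** A length of ICU stay should count time in the ICU. The written rule starts the clock in the ED, so for a patient who goes to a ward and is transferred later, every day before the transfer is recorded as ICU stay. The label describes ICU use. The rule measures ICU use plus the delay in getting there.

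Two things are at stake. First, the reported ICU stay would be too long wherever admission is delayed, and a reader could not tell this from the outcome's name. Second, if the arms differ in how often or how late patients reach the ICU, the comparison of ICU stay would partly reflect that difference. The Discussion says that the 60-minute PaCO2 result will be read together with the secondary outcomes, and ICU stay is one of the few of these that reach beyond the ED.

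**Working it through.** **1. Reading the sentence.** There is one start (date of ED presentation) and there are two ends (ICU discharge, hospital discharge). The word that distributes the terms applies to the two ends, because only one start is given. Hence:

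- hospital stay = hospital discharge date − ED presentation date, which fits its name;
- ICU stay = ICU discharge date − ED presentation date, which does not.

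No other part of the article defines ICU stay or mentions an ICU admission date.

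**2. Does the trial's own size depend on this outcome?** The Sample Size section uses an SD of 6.65%, a margin of 4.3%, one-sided α of 2.5%, 80% power and a 10% allowance for missing data.

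- Per arm: 2 × [6.65 × (1.960 + 0.842) / 4.3]² = 37.54
- With the allowance: 37.54 / 0.9 = 41.7, so 42 per arm and 84 in total.

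The stated figure reproduces, and ICU stay is not among its inputs.

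**3. Error for one patient.** Let D = ICU admission date − ED presentation date, and S = ICU discharge date − ICU admission date. The rule records R = D + S, so the excess is exactly D, or D/S as a fraction of the true stay. The document gives neither D nor S; the values below are assumptions.

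| Delay D (days) | True stay S (days) | Recorded R (days) | Excess D/S |
|---|---|---|---|
| 0 | 4 | 4 | 0% |
| 1 | 4 | 5 | 25% |
| 3 | 4 | 7 | 75% |
| 5 | 4 | 9 | 125% |

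For delays of 1 to 5 days and true stays of 2 to 7 days, the excess runs from 1/7 = 14% to 5/2 = 250%. Because the count uses dates, time in the ED adds a day only if the ICU admission falls on a later date.

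**4. Error in the comparison.** Among patients who reach the ICU, the difference in mean R equals the difference in mean S plus the difference in mean D. If mean delay is the same in both arms, the second term is zero: both arms are inflated and the difference in means is not shifted. If a share p of an arm's ICU patients is delayed by d days, that arm's mean rises by p × d. With 3 in 10 delayed in one arm and none in the other, the spurious difference is 0.3, 0.9 or 1.5 days for d = 1, 3 or 5. With equal shares and equal delays it is 0. These shares are also assumptions.

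**The case against.** **A common origin is defensible.** ED presentation exists for every participant and lies close to randomization, whereas ICU admission comes after it. Time from presentation to ICU discharge is a coherent quantity, and the analysis section permits time-to-event methods. This stands in part: if that quantity is meant, the defect is the name, and renaming cures it. But the outcome is recorded only where applicable, that is, for patients who reach the ICU, so the advantage of an origin shared by all randomized patients is not obtained.

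**The outcome is exploratory, and the sentence may be loose drafting.** Both points are fair and limit the importance. They do not remove the error, because abstractors who follow the written rule would record the wrong quantity. Double data entry and range checks would not flag it, since the entries would agree with the rule.

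**A stronger reading is tempting.** A reader might infer that the rule will produce a false difference between the arms. Suppose 10 patients per arm reach the ICU, each with 3 true ICU days, and 3 in one arm arrive after 4 ward days. The recorded means are (7 × 3 + 3 × 7)/10 = 4.2 against 3.0 days. The document does not support this as a forecast. It gives no ICU admission rate, no transfer delay and no evidence that the device changes the route to the ICU. The example also compares means, whereas the plan allows nonparametric analysis: both medians are 3 days, and an exact rank-sum test gives a two-sided p of 2 × C(10,3)/C(20,3) = 2 × 120/1140 = 0.21. The ranks do shift, so the distortion in that scenario is not zero, but the scenario is only one of many possible.

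**Conclusion.** The definition is wrong as written for the outcome it names, and nothing else in the article corrects it. The excess per patient is exactly the number of calendar days from ED presentation to ICU admission. How large that is in this trial cannot be known from the document; the percentages above rest on assumed delays and stays. Bias between arms is conditional on delayed transfer differing by arm. That is possible in an open-label trial whose Discussion accepts that lack of blinding may affect escalation decisions, but it is not shown. The noninferiority conclusion does not depend on this outcome. The point is a correction to a secondary, exploratory endpoint, to be settled before analysis.

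**What to change.** Split the sentence in Outcome Measures into two definitions:

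- ICU length of stay: ICU admission date to ICU discharge date.
- Hospital length of stay: ED presentation date to hospital discharge date, as now.

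Add the ICU admission date to the items abstracted from the electronic record. If time from presentation to ICU discharge is the intended quantity, keep the rule and rename the outcome accordingly in the text and in Table 1.

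The cost is one sentence and one date field. By July 2026, 19 of 84 participants were enrolled. Because these data are taken from the electronic record after discharge, the admission date should be retrievable for those participants too. How repeated ICU stays are combined is a separate detail that the full protocol or SAP can settle.

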### Sample Size

A total of 84 patients (42 per group) will be enrolled to provide 80% power and one-sided α of 2.5% to demonstrate noninferiority [25] assuming an SD of 6.65% for percentage change in PaCO_2_ levels before and after treatment [26] and a noninferiority margin of 4.3%. The sample size includes an estimated 10% allowance for missing primary end point data. The noninferiority margin of a 4.3% absolute difference in percentage change was informed by clinician judgment (number of specialist accredited [board-certified] emergency physicians, n=14) of clinically acceptable differences and literature on PaCO_2_ responses to NIPPV. For example, emergency physicians opined that a change from 70 mm Hg to 63 mm Hg using HVNI (−10.0%) was considered noninferior to a change in PaCO_2_ from 70 mm Hg to 60 mm Hg after treatment with NIPPV (−14.3%).

### Statistical Analysis Overview

The primary analysis will follow an intention-to-treat approach, with supportive per-protocol analysis excluding major deviations (eg, early crossovers or missing postbaseline ABG values) and a safety set analyzed as treated. The main end point, percentage change in PaCO_2_ at 60 minutes, will be assessed using analysis of covariance (ANCOVA) adjusting for baseline PaCO_2_ and prespecified covariates (eg, etiology, baseline pH, and age). Noninferiority will be concluded if the upper bound of the 2-sided 95% CI for the HVNI–NIPPV adjusted difference is below the 4.3% margin. A prespecified sensitivity analysis will repeat the primary ANCOVA model using absolute change in PaCO_2_ at 60 minutes as the dependent variable to assess whether the conclusions are robust to the choice of relative vs absolute outcome metric. Secondary endpoints (percentage PaCO_2_ changes at 30 minutes, respiratory rate, and modified Borg Dyspnea Scale) will use similar adjusted models, whereas binary outcomes (treatment failure, intubation, and adverse events) will be compared using chi-square or Fisher exact tests and logistic regression, and length of stay and mortality will be assessed via nonparametric or time-to-event and logistic methods. Missing data handling will focus primarily on the primary outcome (percentage change in PaCO_2_ at 60 minutes). Missing 60-minute ABG results may occur due to early treatment crossover, intubation before the 60-minute time point, patient refusal of repeat ABG, or technical failure of the ABG analyzer. Multiple imputation by chained equations will be performed, with the imputation model including baseline PaCO_2_, baseline pH, treatment arm, age, etiology, respiratory rate, and 30-minute PaCO_2_ (if available). A minimum of 20 imputed datasets will be generated, and results will be pooled using the Rubin rules.

Sensitivity analyses will include (1) complete-case analysis (excluding participants with missing primary outcome data) and (2) worst-case imputation for the HVNI arm (assigning the worst observed percentage change to missing values in the HVNI arm and the best observed percentage change to missing values in the NIPPV arm), which is a conservative approach for noninferiority trials. Baseline covariates with missing data (expected to be minimal) will be handled through multiple imputation within the same multiple imputation by chained equations framework. Missing secondary outcomes will be analyzed using available data, with the extent of missingness reported for each outcome. Secondary endpoints will be treated as exploratory without formal multiplicity adjustment.

Prespecified exploratory subgroup analyses will be conducted to assess potential heterogeneity of treatment effect. Subgroups will include (1) COPD vs non-COPD etiology, (2) baseline PaCO_2_ strata (eg, 45‐60 mm Hg vs >60 mm Hg), and (3) baseline pH strata (eg, 7.25‐7.35 vs <7.25). Subgroup effects will be evaluated by including interaction terms (subgroup × treatment) in the primary ANCOVA model. These analyses are exploratory and hypothesis generating; the trial is not powered for subgroup comparisons, and results will be interpreted with caution.

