**Methods:**

This is a single-center, open-label, noninferiority randomized controlled trial conducted in the ED of a tertiary academic center. Adults aged 21 years and above with T2RF, defined as partial pressure of carbon dioxide (PaCO_2_) above 45 mm Hg and pH below 7.35 requiring ventilatory support, will be randomized 1:1 to HVNI via a single-prong cannula or standard NIPPV. Allocation will be concealed via an independent web-based platform using variable block sizes. The primary outcome is percentage change in PaCO_2_ from baseline to 60 minutes after initiation of therapy. A total of 84 patients provide 80% power and one-sided α of 2.5% assuming an SD of 6.65% and noninferiority margin of 4.3%. Analyses will use intention-to-treat and per-protocol approaches, and sensitivity analyses to address missing arterial blood gas results will be conducted. Predefined failure criteria (persistent or worsening acidosis, rising PaCO_2_, refractory hypoxemia, severe intolerance, and clinical deterioration) will trigger crossover or escalation per protocol.

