### Interventions

In the HVNI arm, patients will receive oxygen therapy through the Vapotherm high-velocity therapy 2.0 via a single-prong nasal cannula (Unicorn). Initial settings are flow rate of 35 L per minute [14], temperature of 37 °C, and fraction of inspired oxygen (FiO_2_) titrated up to 1.0 to achieve target oxygen saturation (SpO_2_). The titration algorithm will be to maintain flow rate at 35 L per minute when tolerated to optimize CO_2_ washout. If intolerance occurs (eg, agitation or discomfort), stepwise reduction in flow by 5 L per minute will be performed to the minimally tolerated level while maintaining target SpO_2_. Adjustments in temperature and FiO_2_ will be up to the attending physician’s discretion to achieve the target SpO_2_ value. Flow rate may be uptitrated as tolerated upon assessment of respiratory rate, work of breathing, and comfort. Study investigators will verify that the single-prong cannula remains securely positioned in the nostril and has not been dislodged due to patient movement. Mouth state (open vs closed) will be recorded at each assessment time point as open-mouthed breathing may reduce the effectiveness of nasopharyngeal dead-space washout. If the cannula is found to be displaced, it will be repositioned immediately, and the event will be documented. Persistent inability to maintain cannula position will be recorded as a protocol deviation.

In the NIPPV arm, patients will receive ventilation through the Respironics V60 respirator (Philips Healthcare) with an oronasal mask of appropriate size. Initial settings are IPAP of 12 to 20 cm H_2_O, EPAP of 5 to 10 cm H_2_O, and FiO_2_ of up to 1.0 to achieve the target SpO_2_. The titration algorithm will be to adjust IPAP to alleviate dyspnea and reduce respiratory rate and PaCO_2_, adjust EPAP for oxygenation and to counter intrinsic positive end-expiratory pressure when indicated, and optimize mask fit to minimize leak.

Cointerventions such as bronchodilators, systemic steroids, antibiotics, diuretics, and other standard-of-care therapies are permitted as clinically indicated and should follow departmental protocols. To reduce confounding, all cointerventions will be documented with time stamps. Initiation of major therapy changes will be avoided within 10 minutes preceding scheduled ABG draws when clinically safe.

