### Rescue, Failure, and Crossover Criteria

The independent attending physician may change modality or escalate care if deterioration occurs. To standardize decisions, treatment failure is defined by any of the following: persistent or worsening acidosis (pH decrease ≥0.03 from baseline or pH <7.25 with respiratory rate of >30 breaths per minute after 30 minutes of therapy, PaCO_2_ increase ≥5 mm Hg at 30 minutes compared with baseline, and SpO_2_ persistently below target for >5 minutes despite FiO _2_≥0.8 [or the maximal tolerated settings]), severe intolerance to the device (eg, sustained agitation or inability to tolerate the interface) despite comfort measures, and clinical signs of impending respiratory failure (eg, decreasing consciousness, marked fatigue, and hemodynamic deterioration). Intubation criteria follow departmental standards for acute respiratory failure and will be applied consistently in both arms. All crossovers and intubations will be recorded with timing and reason.

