Exploratory subgroup analyses (eg, COPD vs non-COPD and baseline PaCO_2_ strata) are prespecified and described in the Statistical Analysis Overview section. These analyses are designed to assess potential heterogeneity of treatment effect across clinically relevant subpopulations, recognizing that the trial is not powered for formal subgroup comparisons.

A noninferiority design is appropriate given that NIPPV remains the standard of care for acute T2RF and a more tolerable, operationally streamlined alternative could be clinically valuable. The noninferiority margin of the primary end point (change in PaCO_2_ at a prespecified early time point of 60 minutes) is defined a priori and justified on clinical grounds informed by the expected magnitude of PaCO_2_ improvement with NIPPV in similar populations. Nevertheless, noninferiority trials are inherently vulnerable to bias toward equivalence as factors that dilute true treatment difference, such as protocol deviations and nonadherence, tend to favor noninferiority by minimizing observed differences between interventions [28]. The study protocol seeks to mitigate this risk by incorporating complementary analyses using both intention-to-treat and per-protocol approaches to ensure valid interpretation of noninferiority findings. Predefined rescue criteria for escalation and intubation will be used to reduce performance bias in clinician-driven decisions.

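### The per-protocol set excludes early crossovers, which are largely responses to treatment failure, so it cannot give the protection against false noninferiority that the Discussion claims for it

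*Protocol article*

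**What the plan says.** **Analysis sets.** In the Statistical Analysis Overview, "The primary analysis will follow an intention-to-treat approach", with a "supportive per-protocol analysis excluding major deviations (eg, early crossovers or missing postbaseline ABG values"). The decision rule names one interval: "Noninferiority will be concluded if the upper bound of the 2-sided 95% CI" for the adjusted difference lies below 4.3%.

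**Why patients cross over.** The Abstract says that the predefined failure criteria "will trigger crossover or escalation per protocol". The section on rescue, failure and crossover says: "The independent attending physician may change modality or escalate care if deterioration occurs". One failure criterion is the endpoint variable measured earlier, a PaCO2 "increase ≥5 mm Hg at 30 minutes compared with baseline". Others are worsening acidosis, low saturation, severe device intolerance and clinical signs of impending failure.

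**Why gases go missing.** The Statistical Analysis Overview lists crossover and intubation before 60 minutes among the causes of a missing 60-minute ABG, alongside refusal and analyzer failure.

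**What the set is for.** The Discussion acknowledges that noninferiority trials are prone to bias toward equivalence and says that the protocol mitigates this by "incorporating complementary analyses using both intention-to-treat and per-protocol approaches to ensure valid interpretation of noninferiority findings".

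**The concern.** A per-protocol analysis helps a noninferiority trial only if it removes departures from the plan for reasons unrelated to how the patient responded. Here the two named exclusions remove many patients because they responded badly. A crossover that follows the protocol is counted as a major deviation, and part of the missing-gas exclusion removes the same kind of patient.

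A set filtered on response can make an inferior device look acceptable, because its poor responders have been taken out. Intention-to-treat keeps those patients, but a crossover with an observed 60-minute gas enters with the value reached after rescue. A reader who sees both analyses below the margin would take the second as independent support for the first, and it may not be.

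**Working it through.** **The plan's own figure.** Inputs from the Sample Size section: margin 4.3, SD 6.65, one-sided α 2.5%, power 80%, allowance 10%.

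n per arm = 2 × [6.65 × (1.960 + 0.842) / 4.3]² = 37.5. Dividing by 0.9 gives 41.7, so 42 per arm and 84 in total. The plan's sample size reproduces.

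**Does another analysis of the primary endpoint count a rescued failure as unfavorable?**

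| Analysis | Crossover with an observed 60-minute ABG | Crossover without one |
|---|---|---|
| Intention-to-treat | post-rescue value | multiple imputation |
| Per-protocol | excluded | excluded |
| Complete-case | post-rescue value | excluded |
| Worst-case imputation | post-rescue value | worst observed change (HVNI) or best (NIPPV) |

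None does so for a crossover with an observed gas. Treatment failure and conversion are reported, but only as secondary outcomes treated as exploratory.

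**Size under a 30-minute rule.** Simulation with 42 per arm, SD 6.65, an unadjusted t interval and 8,000 runs (Monte Carlo standard error about 0.2 to 0.3 points for rates of 2.5% to 7%). HVNI is truly 4.3 points worse, so the error rate should be 2.5%. The NIPPV mean is −14.3% and baseline 70 mm Hg, as in the plan's margin example. Not in the documents, and therefore assumed: the 30-minute mean is half the 60-minute mean, the 30/60-minute correlation is 0.7, and every failure is excluded. The 5 mm Hg criterion is 5/70 = +7.1%. Lower cut-offs are not protocol criteria; they stand in for other response-related reasons to switch.

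| Excluded if the 30-minute change is at least | Excluded, NIPPV vs HVNI | Mean difference | False noninferiority |
|---|---|---|---|
| +7.1% in both arms | 2% vs 4% | 4.12 | 3.3% |
| +2% in both arms | 9% vs 15% | 3.84 | 5.0% |
| 0% in both arms | 14% vs 23% | 3.72 | 5.6% |
| −2% in both arms | 22% vs 33% | 3.58 | 6.8% |
| +7.1%, plus intolerance unrelated to PaCO2 (20% NIPPV, 5% HVNI) | 21% vs 8% | 4.13 | 3.4% |
| −2% NIPPV, +2% HVNI | 22% vs 15% | 4.81 | 1.1% |
| −4% NIPPV, +2% HVNI | 32% vs 15% | 5.47 | 0.3% |

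In the last two rows NIPPV has more response-related failures, and the bias turns against HVNI.

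**Upper bound.** Suppose instead that exactly the worst fraction f of the 60-minute values is removed. The arm mean then shifts by SD × φ(z)/(1 − f), where z is the (1 − f) normal quantile: 6.65 × 0.1031/0.95 = 0.72 for f = 5%; 6.65 × 0.1755/0.90 = 1.30 for 10%; 6.65 × 0.2332/0.85 = 1.82 for 15%; 6.65 × 0.2800/0.80 = 2.33 for 20%.

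- HVNI 10%, NIPPV 0%: 4.3 − 1.30 = 3.0; false noninferiority about 14%.
- HVNI 15%, NIPPV 5%: 4.3 − 1.82 + 0.72 = 3.2; about 12% to 14%.
- HVNI 20%, NIPPV 5%: 4.3 − 2.33 + 0.72 = 2.7; about 21% to 24%.

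The ranges reflect whether the fraction is removed as a whole number of patients or by a fixed cut-off.

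**The case against.** Much of the case on the other side stands.

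- **The set is supportive.** The decision rule is not tied to it, so a biased per-protocol result cannot by itself produce a noninferiority claim. A reader might infer that the trial's type I error is 12% to 24%. It is not: those rates belong to the supportive analysis alone, and they assume perfect selection on the 60-minute outcome. The failure criteria act earlier and only partly on PaCO2.
- **The direction is not fixed.** A reader might infer that intention-to-treat and per-protocol both always favor HVNI. Failure includes severe intolerance, and the article's premise is that NIPPV is often poorly tolerated. If NIPPV failures are more frequent and related to response, the bias reverses.
- **Crossovers are not identical to failures.** The physician may switch but need not. Some failures will stay on the device or be intubated.
- **Cannula displacement.** The Interventions section says "Persistent inability to maintain cannula position will be recorded as a protocol deviation". A reader might infer that this filters only the HVNI arm. The text does not call it a major deviation or say that it leads to exclusion, so the inference is not supported.
- **Partial safeguards exist.** Worst-case imputation is severe on HVNI for missing values, and crossovers and intubations are recorded with timing and reason.
- **The exclusions are only examples,** and the full definition may sit in an analysis plan not shown. This does not remove the point. The article names these exclusions and states the purpose of the set, and the two do not fit together.

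**Conclusion.** The point holds in limited form. The per-protocol set, as described, selects on response after randomization and cannot bear the weight that the Discussion puts on it. If HVNI is truly at the margin and failures are driven by gas exchange under one rule for both arms, false noninferiority in this analysis is about 3% to 7% instead of 2.5%. The 12% to 24% range is an upper bound. If NIPPV has more response-related failures, the rate falls below 2.5%.

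The article gives no expected failure or crossover rates, so these figures are a range under stated assumptions and not an estimate for this trial. The harm is false corroboration of the intention-to-treat result. A check whose bias depends on an unknown failure pattern cannot ensure valid interpretation in either direction. This is a worthwhile, inexpensive improvement and not a flaw that invalidates the primary analysis.

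**What to change.** 1. Limit per-protocol exclusions to reasons unrelated to response: ineligible at baseline, assigned device never started, or ABG mistimed or technically invalid. Stop counting protocol-directed crossover or intubation as a major deviation.
2. Add a prespecified sensitivity analysis of the primary endpoint. Patients who cross over, are intubated or meet the failure criteria before 60 minutes receive an unfavorable value, whether or not a 60-minute ABG was obtained. Use the last on-treatment PaCO2 before the switch if there is one. Otherwise use a stated unfavorable value, such as the worst observed change. The fallback is needed because a patient who switches before 30 minutes may have only the baseline gas.
3. Reword the Discussion so that agreement between intention-to-treat and the current per-protocol set is not presented as ensuring valid interpretation.

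Requiring both sets to meet the margin is a debatable convention and is not needed here.

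The cost is wording and a little extra analysis. No patients are added, clinical management does not change, and the data are already to be collected. With 19 of 84 enrolled as of July 2026 and analysis due only after enrollment ends, it can still be prespecified. The downside is that the revised set departs from a conventional as-adhered per-protocol set, which can still be reported as secondary.
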